#### **Primary H3**

BI/RT+ will have positive net social benefits relative to BI/RT alone.

As described above, we will measure social benefits (e.g., downstream medical costs, reduced crime) and costs related to the interventions. We will then test whether marginal costs, marginal benefits, and net benefits of the interventions are different than zero.

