### Patient follow-up procedures and outcome measures

Patients in both the BI/RT and BI/RT+ conditions were asked to complete follow-up assessments every 3 months following baseline for 1 year (i.e., at 3, 6, 9, and 12 months post-recruitment). Assessments took place in person, generally at the health center where the patient was recruited.

Table 2 provides a summary of each of the variables involved in the trial and indicates the relevant purpose of the variable, the instrument used to assess that variable, and the assessment points where the instrument was delivered.

**Table 2 Tab2:** Outcome variables and assessment points

Variable	Purpose	Instrument	Assessment points
Drug and alcohol problems	Screen, randomize	AUDIT, DAST-10	Screening
Intervention and treatment engagement	Hypothesis 1	NSMOS, patient charts	Baseline, 3-, 6-, 9-, 12-months
Drug use and severity	Hypothesis 2	ASI, urinalysis, MINI	Baseline, 3-, 6-, 9-, 12-months
Medical and psychosocial functioning and HIV risk	Hypothesis 3	ASI, HIV-RA, chronic conditions Questionnaire, healthy days	Baseline, 3-, 6-, 9-, 12-months
Readiness to change and personal stress	Covariates	Personal rules, PSS-4	Baseline, 3-, 6-, 9-, 12-months
Patient satisfaction	Evaluation	Client satisfaction form	3-months

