#### Economic evaluation

The economic evaluation has two primary components: (1) a societal-level cost-effectiveness evaluation and (2) a sustainability evaluation.

From a societal perspective, we hypothesize that BI/RT+ will have positive net social benefits relative to BI/RT alone. Net social benefits will be estimated as the difference in the additional benefits in dollar terms for BI/RT+ patients relative to BI/RT patients and additional costs for BI/RT+ patients relative to BI/RT. Benefits assessed will include economic benefits from crime avoided, enhanced job productivity, and downstream medical cost offsets. Costs assessed will include the costs of the intervention, such as fixed clinic costs, time and resources expended by clinic personnel delivering the intervention, and personal costs incurred by participants receiving the intervention (e.g., transportation expenses).

In addition to performing a societal-level economic evaluation, we will also develop a sustainability model for primary care clinics to help inform a decision regarding adoption of BI/RT or BI/RT+ in the future. Inputs for the model will consist of fixed costs for the intervention, such as training and space allocation, as well as variable costs that involve screening yield and productive use of the BHC. We will also model revenue sources and the ability to use codes which allow for billing of the screening. From this model, we will measure outcomes such as time to break-even costs of investing in SBIRT and return on investment in SBIRT for each of the sites included in this study.

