### Data analysis

A total of 600 patients were randomized to the BI/RT or BI/RT+ conditions, and we stratified based on site, behavioral health consultant, and drug or alcohol severity (mild, moderate, or severe based on AUDIT or DAST-10 score). These stratification variables were chosen to account for possible differences in intervention delivery and treatment response. Specifically, we aimed to account for general site differences such as neighborhood/population served, typical amount of clinical contact received by patients, and range of services available. Similarly, we chose to stratify randomization by BHC in order to equalize non-specific provider variables across conditions. Because severity of substance use has consistently been demonstrated to moderate the impact of brief intervention on substance use [13], we equalized the proportion of mild, moderate, and severe substance use across conditions. Prior to performing all analyses, standard data screening/cleaning procedures will be applied. These procedures will (1) re-screen the data for data-entry errors, (2) check for outliers, (3) assess the extent and pattern of missing data, and (4) check that appropriate assumptions of normality are met and employ remedial measures such as power transformations whenever necessary. The randomization will be checked by comparing the groups on relevant background variables and on all baseline dependent measures. The comparisons will use analyses of variance for continuous variables and log-linear models for discrete or ordinal responses. Some covariates will be considered for inclusion in the main analyses to improve the precision of our hypothesis testing [56]. In addition, we have powered the study sufficiently to conduct subgroup analyses. Based on the literature, it is possible that patients who are using harder illicit drugs (cocaine, heroin, etc.) may respond differently to BI/RT and BI/RT+ than patients who are only using marijuana, or who use marijuana but primarily have a problem with alcohol. We will be adequately powered to break out these subgroups for secondary analysis. Below we specify each hypothesis and discuss the statistical procedures we will employ in analyzing the data.

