#### **Primary H2**

Patients assigned to BI/RT+ will demonstrate larger reductions in drug use by point prevalence urine samples and by reported days using over the 12-month follow-up compared to patients in BI/RT.

A generalized estimating equations (GEE) model [58] will be used to compare participants in the two groups on rate of urine-confirmed drug abstinence at each follow-up assessment, and linear mixed effects models will be used to examine days of self-reported drug use in the past 30 days at each follow-up assessment. The models will be similar to those outlined for H1, and the baseline response variable (i.e., urine result or days drug use) will be entered as a covariate in the model. As with H1, contrasts will examine the effects of the intervention separately for the two drug type sub-groups. Analyses will be performed using SAS’s PROC GENMOD (GEE) and PROC MIXED.

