### Power for the primary hypotheses

Power analyses are based on the sub-group contrasts identified for each of the primary hypotheses. The analyses are based on a two sided alpha of .0125 (.05/4 outcome variables–number of treatment sessions attended, urinalysis-confirmed abstinence, days of self-reported drug use, and cost of acute care), an estimated correlation of .5 between the repeated measurements where applicable, and a 20 % attrition rate by month 12. Power calculations were based on Diggle, Heagerty, Liang, and Zeger [58] for the mixed effects models, Hedeker, Gibbons, and Waternaux [59] for the GEE models, and Cohen [60] for the cost-related hypotheses. With a sample size of 100 per condition in the illicit drug sub-group, we will have 80 % power to detect moderate effects of the intervention (*d* = .5) for the mixed effects models and cost-related analysis and 80 % power to detect a 20 % difference between the two groups for the GEE model. With a sample size of 200 per condition in the alcohol/marijuana sub-group, we will have 80 % power to detect smaller effects of the intervention (*d* = .25–.30) for the mixed effects models and cost-related analysis and 80 % power to detect smaller differences (13–15 %) between the two groups for the GEE model.

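### Primary H3 (costs, benefits, net benefit) names no model, baseline value or drug-type contrast; run as a simple two-group comparison it stays valid but loses precision and misses the 80% sub-group power claimed for costs

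*Protocol article*

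**What the plan says.** **H3.** Under Primary H3, social benefits and intervention costs are to be measured, and then: "We will then test whether marginal costs, marginal benefits, and net benefits of the interventions are different than zero". No model, covariate, site/BHC term or drug-type contrast is named.

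**Definition of the quantity.** The Economic evaluation section defines net benefit as the between-arm difference in benefits less the between-arm difference in costs. On the benefit side: "Benefits assessed will include economic benefits from crime avoided, enhanced job productivity, and downstream medical cost offsets". The costs listed are those of delivering and receiving the intervention.

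**The other hypotheses.** H1 has a linear mixed model with group, drug type, time and BHC/site, plus contrasts within each drug-type sub-group. H2 follows that model, and "the baseline response variable (i.e., urine result or days drug use) will be entered as a covariate in the model"; its contrasts are again by drug type. H4 does the same.

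**Data in hand.** Table 2 lists "NSMOS, patient charts Baseline, 3-, 6-, 9-, 12-months" for service use, and the ASI on the same schedule. On randomisation, the Data analysis section says "we stratified based on site, behavioral health consultant, and drug or alcohol severity". The same section says that some covariates will be considered for the main analyses, without naming any.

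**Power.** "The analyses are based on a two sided alpha of .0125", with a 20% "attrition rate by month 12". The cost calculation rests on its own reference, "Cohen [60] for the cost-related hypotheses", separate from those given for the mixed and GEE models. The section says that power is based on the sub-group contrasts for each primary hypothesis. It claims 80% for the cost analysis at d = .5 (100 per condition, illicit drug) and at d = .25 to .30 (200 per condition, alcohol/marijuana).

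**The concern.** H3 is a primary hypothesis, yet an analyst who follows the text as printed could simply take the difference in mean dollars and test it. That leaves unused the baseline service use, the baseline employment and legal information and the randomisation strata. Medical, crime and earnings amounts are usually skewed and tend to persist within a person, so an analysis that ignores their baseline values is noisier than it needs to be. Where site, BHC or severity predicts cost, a test that ignores strata used in randomisation also has a standard error that is too large.

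The two sections do not fit together either. The power section relies on sub-group contrasts for costs, but the H3 section identifies none. If the simple comparison cannot deliver the stated 80%, the choice of H3 analysis decides whether the cost contrasts are adequately powered.

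**Working it through.** **Inputs from the Power section.** Two-sided alpha .05/4 = .0125; 100 and 200 per condition; 20% attrition, giving 100 × .8 = 80 and 200 × .8 = 160 analysed per arm; d = .5, and d = .25 to .30; claimed power 80%.

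**Assumptions.** The cost analysis is read as a two-sample comparison of means. The correlation r between baseline and follow-up dollars is not documented for costs. The plan's .5 is stated for repeated measurements where applicable, so r is varied here from .2 to .5.

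**Step 1: the plan's own figure.** Detectable d at 80% power (normal approximation) is (2.498 + 0.842) × √(2/n) = 3.339 × √(2/n).

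| n per arm | detectable d | d stated |
|---|---|---|
| 100 | .472 | .5 |
| 80 | .528 | .5 |
| 200 | .334 | .25–.30 |
| 160 | .373 | .25–.30 |

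In the illicit drug sub-group, d = .5 is reached only if attrition is ignored. In the alcohol/marijuana sub-group, .25 to .30 is not reached with or without attrition. The range does reproduce for the mean of four repeated measures at correlation .5. The variance factor is then (1 + 3 × .5)/4 = .625, and detectable d is .334 × √.625 = .264 (200 per arm) or .373 × √.625 = .295 (160 per arm). So the stated range suits the mixed models and not a single cost comparison.

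**Step 2: power of the simple comparison** (noncentral t, noncentrality d√(n/2), 2n − 2 degrees of freedom).

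- 100 per arm, d = .5: 84.4%. After attrition, 80 per arm: 73.7%.
- 200 per arm: 68.8% at d = .30 and 49.7% at d = .25. After attrition, 160 per arm: 56.8% and 39.3%.

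**Step 3: with baseline adjustment.** The residual variance is multiplied by 1 − r², so d is replaced by d/√(1 − r²). At r = .5 the factor is .75.

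| r | 80/arm, d = .5 | 160/arm, d = .30 | 160/arm, d = .25 |
|---|---|---|---|
| none | 73.7% | 56.8% | 39.3% |
| .2 | 75.7% | 59.0% | 41.0% |
| .3 | 78.4% | 61.8% | 43.4% |
| .4 | 82.1% | 66.1% | 47.2% |
| .5 | 86.8% | 72.1% | 52.9% |

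The gain is about 2 points at r = .2 (2.0, 2.2, 1.7), 4 to 5 at .3 (4.7, 5.0, 4.1) and 13 to 15 at .5 (13.1, 15.3, 13.6). The d = .30 contrast needs r of about .6 to reach 80%.

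These gains apply to the benefit components, and to net benefit as far as those components drive its variance. Intervention cost has no baseline counterpart and gains nothing from this step. Any gain from the strata would be additional and is not quantified.

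**The case against.** **The text never says the test is unadjusted.** This stands. A reader might infer that the plan fixes a raw two-sample test, but the H3 section is silent, and the Data analysis section leaves covariates open before introducing all the hypotheses. The power loss is conditional on how the sentence is carried out.

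**An article may leave the economic model to the full protocol or analysis plan.** That is fair for the link function and the bootstrap. It is less persuasive for a primary hypothesis in an article that prints models and contrasts for H1, H2 and H4. It also does not settle the mismatch between the power section's sub-group claim for costs and an H3 section with no sub-group contrast.

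**H3 is not unique in every respect.** H1 also names no baseline value, and no analysis names severity. What is particular to H3 is that no model, no BHC/site term and no drug-type contrast is given.

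**No bias is at issue.** A reader might infer that pre-existing cost differences would be counted as an effect of BI/RT+. Under randomisation, chance imbalance is sampling variance, and the unadjusted standard error already includes it. Ignoring the strata makes the test conservative but not invalid.

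**The size rests on a correlation that the plan does not give for costs.** This also stands, so the range matters more than the figure at .5. The power section's fourth outcome is acute care cost and not net benefit, so its figures map only loosely onto the three H3 tests. It assigns the cost analysis the same d and power as the mixed models, so it does not itself present cost power as the weakest.

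**Conclusion.** The point holds as a matter of precision and internal consistency. H3 is the one primary hypothesis without a named model. Carried out as a simple two-group comparison, it is valid but reaches about 74% power in the illicit drug sub-group and 39% to 57% in the alcohol/marijuana sub-group, against the 80% claimed.

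The shortfall assumes a two-sample comparison of means with 20% attrition at alpha .0125. How much adjustment recovers depends on an undocumented correlation. At .2 or .3 none of the three contrasts reaches 80%. At .5 only the d = .5 contrast does, and the alcohol/marijuana contrasts stay at 53% to 72%. Adjustment is therefore worthwhile but does not by itself rescue the stated power, which is why the cost power must also be restated. The documents do not show that an unadjusted test was chosen, or that the estimate would be biased.

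**What to change.** In the Primary H3 section, state that the arm difference in mean dollars will be estimated by patient-level regression with an identity link, as follows.

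- **Terms for all outcomes:** arm, drug type, arm by drug type, site/BHC and severity.
- **Baseline terms for benefits and net benefit:** the baseline value of the benefit components (medical, crime, productivity), priced from baseline NSMOS and ASI with the unit prices used at follow-up.
- **Intervention cost:** adjust for the design factors only, since it has no baseline value.
- **Inference:** robust or bootstrap standard errors, because the amounts are likely to be skewed.
- **Reporting:** the arm contrast overall and within each drug-type sub-group, with the raw difference as a sensitivity analysis.

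In the Power section, restate the cost power for this analysis, giving the assumed baseline-to-follow-up correlation and a range around it.

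The cost is analysis-plan wording and one extra pricing step on data already collected; no new patients, visits or instruments are needed. The baseline recall window may be shorter than the 12-month follow-up. That would lower the correlation and the gain but would not bias the randomised comparison.

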#### **Secondary H4**

Patients assigned to BI/RT+ will demonstrate better medical, employment, legal, and psychiatric functioning, as well as reduced HIV risk over the 12-month follow-up compared to patients in BI/RT.

Linear mixed effects models will be used to compare participants in the two groups on measures of psychosocial functioning as assessed by the standard summary scores of the ASI (Medical, Employment, Legal, and Psychiatric) at each follow-up assessment. We will also calculate an overall HIV risk score as assessed by the HIV-RA at each follow-up point. The models will be similar to those outlined for H1, and the baseline response variable will be entered as a covariate in the model. As with H1, contrasts will examine the effects of the intervention separately for the two drug type sub-groups.

### Power for the primary hypotheses

Power analyses are based on the sub-group contrasts identified for each of the primary hypotheses. The analyses are based on a two sided alpha of .0125 (.05/4 outcome variables–number of treatment sessions attended, urinalysis-confirmed abstinence, days of self-reported drug use, and cost of acute care), an estimated correlation of .5 between the repeated measurements where applicable, and a 20 % attrition rate by month 12. Power calculations were based on Diggle, Heagerty, Liang, and Zeger [58] for the mixed effects models, Hedeker, Gibbons, and Waternaux [59] for the GEE models, and Cohen [60] for the cost-related hypotheses. With a sample size of 100 per condition in the illicit drug sub-group, we will have 80 % power to detect moderate effects of the intervention (*d* = .5) for the mixed effects models and cost-related analysis and 80 % power to detect a 20 % difference between the two groups for the GEE model. With a sample size of 200 per condition in the alcohol/marijuana sub-group, we will have 80 % power to detect smaller effects of the intervention (*d* = .25–.30) for the mixed effects models and cost-related analysis and 80 % power to detect smaller differences (13–15 %) between the two groups for the GEE model.

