**Aim 1:** To conduct a randomized controlled trial to address the following ***Primary Hypotheses***:

### **H1**

Patients assigned to BI/RT+ will attend more substance intervention and specialty treatment sessions outside of the FQHC over the 12-month follow-up than patients assigned to BI/RT.

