#### **Primary H1**

Patients assigned to BI/RT+ will attend more substance intervention and community-based specialty treatment sessions outside of the FQHC over the 12-month follow-up than patients assigned to BI/RT.

A linear mixed effects model [57] will be used to compare participants in the two groups on the number of sessions attended in the past 90 days at the 3-, 6-, 9-, and 12-months follow-up assessments. The model will include terms for intervention group, drug type (i.e., illicit drug or alcohol/marijuana), time, BHC/site, and relevant interactions along with any necessary covariates. For these analyses we will combine alcohol and marijuana use given the high prevalence of co-occurring use as well as the social acceptability and decriminalized status of marijuana in Philadelphia, which can contribute to a decreased perception for need for treatment. Specific contrasts will compare (1) differences between individuals in the illicit drug sub-group who received the BI/RT intervention and those who received the BI/RT+ intervention and (2) differences between individuals in the alcohol/marijuana sub-group who received the BI/RT intervention and those who received the BI/RT+ intervention. The mixed effects model will be performed using SAS’s PROC MIXED.

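### H1 and H2 concern all randomised patients, but no all-patient contrast is designated primary, defined or powered; only two sub-group contrasts are, and the article elsewhere calls that sub-group analysis secondary

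*Protocol article*

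**What the plan says.** All references are to the protocol article.

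- **Hypotheses.** Primary H1 reads "Patients assigned to BI/RT+ will attend more substance intervention and community-based specialty treatment sessions outside of the FQHC over the 12-month follow-up" than those assigned to BI/RT. Primary H2 is worded the same way for drug use: "Patients assigned to BI/RT+ will demonstrate larger reductions in drug use by point prevalence urine samples". Neither is limited to a drug type.
- **Model.** Under Primary H1, a linear mixed model "will be used to compare participants in the two groups on the number of sessions attended in the past 90 days". Its terms are given: "The model will include terms for intervention group, drug type (i.e., illicit drug or alcohol/marijuana), time, BHC/site, and relevant interactions". Primary H2 uses similar models, with a GEE for the urine outcome.
- **Named contrasts.** Primary H1 names two: BI/RT against BI/RT+ among illicit-drug users, and the same among alcohol/marijuana users. Primary H2 follows: "contrasts will examine the effects of the intervention separately for the two drug type sub-groups".
- **Power.** The section on power for the primary hypotheses states "Power analyses are based on the sub-group contrasts identified for each of the primary hypotheses". It gives figures for 100 per condition (illicit drug) and 200 per condition (alcohol/marijuana) only.
- **Status of the sub-groups.** The opening paragraph of Data analysis says "We will be adequately powered to break out these subgroups for secondary analysis".

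**The concern.** The article does not settle which test decides H1 and H2. The hypotheses and the general model description point to the comparison of all 600 patients. The named contrasts and the power section point to two separate sub-group comparisons, and the Data analysis section calls the sub-group break-out secondary.

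If the sub-group contrasts decide, three things follow. Each outcome is tested twice at .0125. A result significant in one drug type and not in the other has no stated reading. The comparison that uses every randomised patient, and so has the most power against an effect shared by both drug types, is not the deciding test. A split pair also invites the conclusion that BI/RT+ works for one drug type only, even when the true effect is the same in both.

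**Working it through.** **Inputs from the power section:** two-sided alpha .0125 (.05/4), correlation .5 between repeated measures, 20% attrition by month 12, 100 per condition (illicit) and 200 per condition (alcohol/marijuana), so 300 per condition overall. There are four follow-up visits (3, 6, 9 and 12 months).

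**Assumptions added here:** attrition is linear (95, 90, 85 and 80% retained), dropout is monotone, the correlation is the same between all visits, and the effect is averaged over the visits. Normal approximation throughout.

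**The plan's own 80% figures.** A simpler calculation keeps only the 80% retained to month 12 and uses the mean of four visits, with variance factor (1 + 3 × .5)/4 = .625.
- Alcohol/marijuana, 160 per condition: d = .30 gives 81.5%, which reproduces the plan; d = .25 gives 63%.
- Illicit drug, 80 per condition: d = .5 gives 93%. A single time point gives 75% with 80 per condition and 85% with 100.

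No single method returned 80% in both sub-groups. Results are therefore shown both by direct calculation and at the stated 80% each.

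**Direct calculation.** A patient seen at m visits contributes m/(1 + (m − 1) × .5), that is 1, 1.333, 1.5 and 1.6 for m = 1 to 4. The shares are 5% each for m = 0, 1, 2, 3 and 80% for m = 4:

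info = .05 × (0 + 1 + 1.333 + 1.5) + .80 × 1.6 = 1.472

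SE = √(2/(n × info)), which is .1166 for n = 100, .0824 for n = 200 and .0673 for n = 300.

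Power = P(Z > 2.498 − d/SE).

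The two sub-groups are independent, so both significant = p1 × p2, and exactly one = p1(1 − p2) + p2(1 − p1).

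| Common true d | All-patient | Illicit | Alcohol/marijuana | Both | Exactly one |
|---|---|---|---|---|---|
| .20 | 68% | 22% | 47% | 10% | 48% |
| .25 | 89% | 36% | 70% | 25% | 56% |
| .30 | 97% | 53% | 87% | 46% | 48% |
| .35 | >99% | 69% | 96% | 67% | 32% |

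**At the plan's own design effects** (d = .5 illicit; d = .25 or .30 alcohol/marijuana):
- Direct calculation: illicit power 96%, alcohol/marijuana 70% or 87%. Both significant in 68% or 84% of trials, exactly one in 31% or 15%.
- At the stated 80% each: both .8 × .8 = 64%; exactly one 2 × .8 × .2 = 32%.

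**The group term already in the model.** If a group-by-drug-type interaction is included and the drug types are weighted equally, SE = √(.25 × .1166² + .25 × .0824²) = .0714. Power is 84% at d = .25, against 89% with weights of 1:2, and 62% against 68% at d = .20.

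**Type I error.** If significance in either sub-group counts as support, the error per outcome is 1 − (1 − .0125)² = .0248, about twice the allotted .0125.

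**Detectable all-patient effect.** At 80% power, (2.498 + .842) × .0673 = .225. The simpler method gives .22 with no attrition (300 per condition) and .24 with 240 per condition.

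**The case against.** A reader might infer that no stated test answers H1 or H2. That goes too far. Primary H1 and Primary H2 both describe a comparison of the two randomised groups, and the model has an intervention-group term. Under a common effect of d = .25, an equally weighted version of that term loses only about 5 points of power to the weighted contrast. The larger losses arise only if the sub-group contrasts decide the hypotheses: 89 − 70 = 19 points and 89 − 36 = 53 points for the single contrasts, and 89 − 25 = 64 points for both.

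A reader might also infer that a split pair is the likeliest outcome. That holds only for a common effect of about d = .20 to .30, and at .30 it is nearly a tie with both significant (48% against 46%). The plan does not assume a common effect. It designs for a larger effect in the illicit-drug group and expects response to vary by substance. At its own design effects both contrasts are usually significant.

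There is a coherent benign reading: the two-group comparison is primary, the sub-groups are secondary, and the trial was sized on the smaller, more demanding contrasts. On that reading the all-patient comparison has over 99% power at the design effects. The sub-groups listed in Data analysis are also not worded exactly as the two-way split under Primary H1. Weights and estimation statements are commonly left to the analysis plan.

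These points limit the size of the problem but do not remove it. The benign reading has to be supplied by the reader, because the power section ties the primary hypotheses to the sub-group contrasts and gives no all-patient figure. That tension is in the article's own text and is not a detail left out by condensing.

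**Conclusion.** The point holds as an unresolved question of which test is primary. The article describes an all-patient comparison but does not designate it as primary, define it alongside the drug-type and time interactions, or power it. It powers two sub-group contrasts as the basis of the primary hypotheses and elsewhere calls such a break-out secondary.

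The design is not invalidated, and 600 patients are ample for an all-patient test. The cost lies in interpretation: a chance of a split result with no rule for it of roughly one in seven to one in three at the plan's design effects, rising to about one half under a modest common effect. If either contrast may count as success, the error per outcome is about .025. The power figures rest on the plan's alpha, correlation and attrition, on linear dropout, and on a visit-averaged effect; the common effects of d = .20-.30 are illustrative.

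**What to change.** Reconcile Primary H1, Primary H2 and the power section with the Data analysis paragraph:

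1. For H1 and for each H2 outcome, name one all-patient BI/RT+ versus BI/RT contrast as the primary test at .0125. Average it over the four visits and weight the drug types by their share of randomised patients. It comes from the mixed model or GEE already planned.
2. Keep the two drug-type contrasts as secondary analyses, reported with confidence intervals.
3. State the all-patient detectable effect (about d = .22-.24 at 80% power with 300 per condition) beside the sub-group figures.

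If sub-group primaries are really intended, H1 and H2 should instead be restated by sub-group, with a decision rule for split results and an alpha that covers both tests.

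The cost is wording and one estimation statement per model, with no new patients or data. The downside is small: an effect confined to one drug type is diluted in the primary contrast and would appear as a secondary result.

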### Subject population and setting

A total of 10,935 patients were screened, and 600 eligible individuals were recruited to participate. All participants were patients at three primary care clinics in the Philadelphia metro area. The three clinics in this study are all FQHCs serving traditionally underserved populations, including many low-income and uninsured patients. In addition to providing primary care, the FQHCs offer supportive services such as case management, health education, and prevention using an interdisciplinary approach. The study primarily included adults over the age of 21, but older adolescents (i.e., 18–21 years) were not excluded. All three of the FQHCs are located in neighborhoods of Philadelphia that have greater minority representation than is found for the city as a whole. Our sample was approximately 82 % Black, 7 % White, and 12 % other races. About 8 % were Hispanic and approximately 45 % of our participants were women; the average age was 40. About 30 % were employed either full-time or part-time, 66 % were never married, 11 % were married or cohabitating, and 75 % had at least a high school diploma or equivalent. There was a fairly even split of primary substance use; 35 % of participants primarily used alcohol, 38 % marijuana, and 27 % other substances.

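### If the illicit drug sub-group is defined by primary substance, it has about 81 patients per condition, not 100; the 80% power then fails for cost and, at mid-range abstinence rates, for urine

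*Protocol article*

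**What the plan says.** The section Power for the primary hypotheses bases power on the sub-group contrasts. "The analyses are based on a two sided alpha of .0125 (.05/4 outcome variables"), with "an estimated correlation of .5 between the repeated measurements where applicable, and a 20 % attrition rate by month 12".

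- **Illicit drug sub-group.** The premise is "With a sample size of 100 per condition in the illicit drug sub-group, we will have". The power claimed on it is 80%, for d = .5 in the mixed models and the cost comparison, and for a 20-point gap in urine-confirmed abstinence. No base abstinence rate is given.
- **Alcohol/marijuana sub-group.** "With a sample size of 200 per condition in the alcohol/marijuana sub-group", the detectable effects at 80% power are d = .25–.30 (mixed models and cost) and 13–15 points (urine).

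The section Subject population and setting describes the recruited sample of 600: 35% "primarily used alcohol, 38 % marijuana, and 27 % other substances". The section Data analysis says "we have powered the study sufficiently to conduct subgroup analyses" and then repeats that the drug-type sub-groups can be broken out with adequate power.

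**The concern.** The planned split of 100 and 200 per condition means one third of the 600 in the illicit sub-group. The article reports a completed sample in which 27% had a primary substance other than alcohol or marijuana. The power statement is in the future tense and is not reconciled with that figure.

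The illicit contrast matters. The Background argues that single-session brief intervention has not worked for illicit drugs and that more intensity might. The contrast is specified within primary hypotheses H1 and H2. A null urine or cost result there, read against a claimed 80% power, would look like stronger evidence against a moderate effect than the sample can give.

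**Working it through.** **Inputs from the article.** 600 randomised, allocated half and half; 27% other substances; two-sided alpha .0125 (z = 2.498); 80% power (z = 0.842); correlation .5; four follow-ups; 20% attrition by month 12.

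**Sub-group size by primary substance.**
- Illicit: .27 × 600 = 162; 162/2 = 81 per condition; 81 × .8 ≈ 65. Rounding of 27% allows 79.5–82.5 per condition before attrition.
- Alcohol/marijuana: 600 − 162 = 438; 438/2 = 219 per condition; 219 × .8 ≈ 175.

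**Formulas**, with n analysed per condition:
- Cost: two-sample t-test, one value per patient.
- Mixed models: power = Φ(d·√(n/(2f)) − 2.498), where f = (1 + 3 × .5)/4 = .625 is the variance factor for the mean of four measurements.
- Urine: power = Φ((p2 − p1)/√(f[p1(1−p1) + p2(1−p2)]/n) − 2.498). This is unadjusted and uses unpooled variance; a pooled variance gives about two points less.

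**The article's own figure, 100 per condition (80 after attrition).**
- Mixed models, d = .5: .5 × √(80/1.25) − 2.498 = 1.502, power 93%. The stated 80% is conservative.
- Urine: 80% for 30% v 50% and 78% for 40% v 60%. The stated 80% reproduces at mid-range rates.
- Cost, d = .5: 84% with no attrition, 74% with 80 analysed.

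**At 81 per condition (65 after attrition).**

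| Illicit contrast | No attrition (81) | After 20% attrition (65) |
|---|---|---|
| Cost, d = .5 | 74% | 63% (62.5%) |
| Urine, 40% v 60% | 79% | 67% |
| Urine, 30% v 50% | 80% | 70% (69.5%) |
| Urine, 20% v 40% | 86% | 77% |
| Urine, 10% v 30% | 95% | 89% |
| Mixed models, d = .5 | 94% | 86–87% |

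Example, 40% v 60% with 65: √(.625 × .48/65) = .0679; .2/.0679 − 2.498 = .446; Φ(.446) = 67%.

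**Splitting the cost gap.** From 80% to 73.7% (planned 100, after attrition) is about 6 points. From 73.7% to 62.5% (81 instead of 100) is about 11 points.

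**Effects detectable with 80% power after attrition.**
- Illicit (65): cost about .59; mixed models 3.339 × √(1.25/65) = .46; urine about 23 points centred on 50% (.226, against .204 with 80 analysed).
- Alcohol/marijuana (175): cost about .36; mixed models 3.339 × √(1.25/175) = .28; urine about 14 points centred on 50%.

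The alcohol/marijuana cost figure lies outside the stated .25–.30 although that group exceeds plan. Even 200 per condition with no attrition gives about .33.

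**The case against.** **Membership is open.** The 27% counts primary substance; the article does not say that it is the analysis sub-group. The H1 model names the factor only as illicit drug or alcohol/marijuana. The Data analysis section sets users of harder drugs against those using only marijuana, or marijuana with a primary alcohol problem, and the eligibility table also sorts by use. If any illicit use counts, only 38 of the 438 primary alcohol or marijuana users (8.7%) need such use for the group to reach 200. The Discussion, which contrasts harder-drug users with those primarily using marijuana or alcohol, favours the primary-substance reading. This objection stands as a condition on the point.

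**Urine depends on inputs not given.** At low base rates power stays above 80%. H2 also enters the baseline urine result as a covariate. If baseline correlates r with each follow-up, the variance factor becomes roughly .625 − r². For 40% v 60% with 65 per condition, power is then about 75% at r = .3, 82% at r = .4 and 90% at r = .5. These r values are assumptions, since the article does not say whether its .5 extends to baseline. Applying 20% loss at every visit is also harsh, because the article puts it at month 12 and the model uses earlier visits. All this stands: the urine shortfall is conditional, and about 2 points of detectable difference.

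**The power statement is conditional.** It starts from 100 per condition and is roughly reproducible on that basis for urine. That is fair. The defect is that the article also reports the realised sample and does not reconcile the two.

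**Conclusion.** The point holds conditionally. With membership by primary substance and an even split within drug type (drug type is not a listed stratification factor), the illicit sub-group has about 81 per condition, 19% below the 100 assumed.

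- **Cost:** below 80% with or without attrition, at about 74% and 63%. The sub-group size explains only part of this.
- **Urine, unadjusted:** about 67–70% after attrition at assumed control abstinence of 30–40%, about 77% at 20% v 40%, and above 80% at 10% v 30% or with a strongly predictive baseline covariate.
- **Mixed models (sessions, days of use):** still above 80%.

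A reader might infer that the illicit sub-group is underpowered throughout, or that 80% power for urine and cost is lost outright because too few illicit users were recruited. The article does not support either reading. Two of its four primary outcomes keep their claimed power, membership and the base rate are unstated, and the cost figure was already short after attrition at the planned size.

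**What to change.** 1. State whether sub-group membership is by baseline primary substance or by any illicit use, and give the realised count per condition.
2. Restate power on those counts, naming the base-rate and attrition assumptions and whether the baseline covariate is used. By primary substance, after 20% attrition, the detectable effects at 80% power are:
   - illicit: about d = .59 cost, d = .46 mixed models, 23 points urine at mid-range rates;
   - alcohol/marijuana: about d = .36 cost, d = .28 mixed models, 14 points urine at mid-range rates.
3. Correct the cost claim in both sub-groups; updating the counts alone does not restore it.
4. In Data analysis, qualify the statement of adequate sub-group power for the illicit cost and urine contrasts.

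If membership is by any illicit use, the figures in step 2 must be recalculated from that count. The cost is a few sentences of text and somewhat less favourable figures. Design, conduct and planned analyses do not change.
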